**Study Synopsis**

Study Code Number: RESCUE COPD 001

REC Number 15/SC/0216

UKCRN Number PHT/2015/39

Title of the Trial A randomised controlled feasibility trial of E-health platform Supported Care vs Usual care after Exacerbation of COPD

Development Phase: Exploratory Clinical

Principle Investigator: [name]

Sponsor: Portsmouth Hospitals NHS FT

Purpose of Clinical Trial To assess the feasibility of undertaking a randomised controlled trial to determine the effectiveness of E-health platform Supported Care in improving patients outcomes after exacerbation of COPD

Objectives Usability of platform  
Symptom Control  
Inhaler technique  
Treatment adherence  
Quality of Life

Trial Design: A two parallel arms non-blinded randomised controlled feasibility trial

Planned Trial Period: Participant follow up: 90 days approximately  
Recruitment Period 6 months

Intervention (description, frequency, details of delivery) The study will deliver two interventions one to each arm of the study. One group will be randomised to myCOPD an online self management system and the other group to a conventional written self management plan. Details of the interventions can be found on pages 14 and 15 and Appendix 3 of this protocol.

Outcomes: Trial feasibility outcomes:

- Recruitment rate
- Withdrawal and loss to follow-up rate
- Usability of the of E-health platform

- Use of the of E-health platform
- Completeness of data collection

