**Intervention effectiveness outcomes**

- The time to a two-point improvement in the COPD Assessment Tool (CAT) Score
- The improvement in CAT score at study completion 90(+/- 7) days in the MyCOPD support population compared to usual care
- The number of critical errors by inhaler at study completion 90(+/- 7)
- St Georges Respiratory Questionnaire (SGRQ) score at study completion 90(+/- 7)
- Modified MRC dyspnoea score at study completion 90(+/- 7)
- Patient Activation Measure (PAMs) score at study completion 90(+/- 7)
- Hospital Anxiety and Depression Score (HADS) at study completion 90(+/- 7)
- WPAI score at study completion 90 (+/- 7)
- VSAQ score at study completion 90 (+/- 7)
- COPD treatment adherence (what would be monitored and how would this be measured?)
- The number of exacerbations by study completion 90(+/- 7) days
- The time to exacerbations
- The rate of and timing of antibiotic use by study completion 90(+/- 7) days
- The rate of and timing of steroid use by study completion 90(+/- 7) days
- Safety the number of AEs and SAEs by study completion 90(+/- 7) days

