#### **Visit 4 – Study Completion**

At 90 days after the initial study (enrolment) visit (+/- 7 days) the patient will attend the study site or be visited for the final assessment. This assessment will include the same measures as Visit 1.

- Record clinical data
- SAEs AEs and exacerbations
- Unscheduled health care use
- CAT score
- mMRC
- HAD
- PAM
- SGRQ
- WPAI
- VSAQ
- Inhaler technique assessment
- A practitioner blinded to the intervention arm will perform assessment of inhaler technique videos. They will use the critical error list to evaluate technique.

After PROMs are completed patients will be asked to feedback to the researcher on the platform used in the study, any suggestions for improvement in design and reflections on how the platform affected their self-care decisions during the study. These inputs will be written down as free text and recorded and/or videoed. The study team will then collect the loaned computer tablets from those participants randomised to the myCOPD arm and deliver conventional written self management plans to those participants.

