### **Statistical Section** 

#### **Randomisation**

Patients will be randomised to MyCOPD E-health platform or written self-support platform at the end of visit 1. Randomisation will take place using permuted blocks in a ratio of 1:1 to either platform MyCOPD or written plan (Standard of Care).

Once a patient is consented, all baseline data collected and eligibility confirmed, a study staff will randomise participants to the study using an online randomisation system developed and hosted by my mhealth Ltd.

As this is a web based tool the study staff member will log in to the website using their unique user code and password. They will then enter the participants screening number, initials and the date of the visit. This will then generate a unique randomisation number and inform the user, which study arm the participant will receive either written SMP or online SMP.

Emergency code break will not be required in this study, due to the nature of the intervention.

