The mean difference in the number of critical errors between arms will be estimated by fitting a Poisson regression model. If there is over dispersion due to a high number of zero errors then a zero-inflated Poisson regression model will be used or an over dispersion parameter will be included into the model.

The mean difference in St Georges Respiratory Questionnaire, Modified MRC dyspnoea, PAMs and Hospital Anxiety and Depression between arms at the

final study visit will be estimated using analysis of covariance model including the baseline value of the score as well intervention arm as a covariate in the model. Time to exacerbation will be analysed in a similar manner to the two point increase in CAT score.

The number of adverse events (AE) and serious adverse events (SAE) will be tabulated by arm for each event and also by the number of patients reporting an event. No dictionary for coding adverse events will be used. Events will be recoded using terms of the clinical investigators choosing.

A full statistical analysis plan will be drawn up and agreed by the PI and study team prior to the final data extraction.

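### The per-event adverse event table uses freely chosen terms with no dictionary or grouping rule, so its rows by arm (not the totals) can be split or merged by wording

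*Protocol*

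**What the plan says.** Four parts of the protocol bear on this.

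- **Tabulation.** Under Statistical Methods, the numbers of AEs and SAEs "will be tabulated by arm for each event and also by the number of patients reporting an event".
- **Terms.** The same paragraph continues: "No dictionary for coding adverse events will be used. Events will be recoded using terms of the clinical investigators choosing".
- **Blinding.** The Study Synopsis describes the design as "A two parallel arms non-blinded randomised controlled feasibility trial". In the Randomisation part of the Statistical Section, the online system will "inform the user, which study arm the participant will receive either written SMP or online SMP", the user being a member of study staff. The only blinded step described is under Visit 4: "A practitioner blinded to the intervention arm will perform assessment of inhaler technique videos".
- **Outcome.** The listed safety outcome is "Safety the number of AEs and SAEs by study completion 90(+/- 7) days", and the synopsis says that AEs will be reported descriptively.

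No common list of terms, grouping rule or arm-blind review of event terms appears anywhere in the protocol. The paragraph does not leave coding open for a later plan. It rules out a dictionary and names the investigators' choice of terms in its place.

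**The concern.** A table with one row per event and one column per arm can be read only if the same clinical event always carries the same term. The protocol asks for that table and removes the usual means of achieving consistent terms, without putting another in its place.

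Two things can then go wrong in the rows. Synonyms for one event can fall in separate rows, which dilutes a difference between arms. Unlike events can also be brought under one term, which can hide or create a difference. If whoever chooses the term knows the allocation, neither error need be the same in both arms.

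The stake is modest but real. Aims and Objectives says the safety of the intervention will be reported and that the findings will contribute to larger studies. A descriptive safety table is read row by row, and with 30 patients per arm each row is likely to hold few events.

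**Working it through.** The protocol states no AE rate or AE figure, so there is none to reproduce. The check has three parts.

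**1. Do both readings of *recoded* leave the problem?**

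| Reading of the sentence | What happens to the rows |
|---|---|
| Misprint for *recorded* | Free-text terms go straight into the table, and synonyms form separate rows |
| Literal: terms are chosen again after recording | Synonyms may be joined, but without a stated rule, so unlike events may be joined too |

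The two readings differ in the direction of error, but neither gives consistent rows.

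**2. Which summaries depend on wording?**

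- Total AEs and total SAEs per arm: no. Relabelling an event does not change the count. Seriousness is set by the outcome criteria under Serious Adverse Events, not by the term.
- Patients with any event per arm: no, for the same reason.
- Events, or patients, per term per arm: yes.

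**3. How large can the effect on a row be?** The input from the protocol is n = 30 per arm (Sample size rationale). The event counts are assumed and are not in the document. For proportions p1 and p2:

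difference d = p1 − p2; SE = √[p1(1 − p1)/30 + p2(1 − p2)/30]; 95% CI = d ± 1.96 × SE.

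*One common term, 9/30 v 3/30.* d = 0.300 − 0.100 = 0.200. SE = √(0.0070 + 0.0030) = 0.100. The CI is 0.4 to 39.6 percentage points.

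*Same patients, spread evenly over three synonyms in both arms.* Each row is 3/30 v 1/30. d = 0.100 − 0.033 = 0.067. SE = √(0.0030 + 0.0011) = 0.064. The CI is −5.8 to 19.2 points, three times over.

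*Same patients, spread over three synonyms in one arm only.* If the other arm's 3 all fall under one of those synonyms, the rows are 3 v 3 (0 points), 3 v 0 and 3 v 0 (10 points each, CI −0.7 to 20.7).

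*Equal rates, uneven wording.* With 6/30 in both arms, one term in one arm and an even split over three in the other, the shared row reads 6/30 = 20% v 2/30 = 6.7%. A difference appears where there is none.

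These Wald intervals are rough at such counts and serve only to show scale. Fisher's exact test gives p = 0.10 for 9/30 v 3/30, although the Wald interval just excludes zero, and p = 0.61 for 3/30 v 1/30.

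In every case the arm totals are unchanged: 9 v 3 in the first three examples and 6 v 6 in the last.

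**The case against.** The strongest case against runs as follows.

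- **The listed safety outcome is a count of AEs and SAEs, and counts are immune to wording.** This stands, and it limits the point to the per-event rows. A reader might infer that the whole safety comparison between arms depends on wording. The documents do not support that, because totals and patients with any event are fixed whatever the terms.
- **AEs are only to be described, so per-row p-values measure a loss nobody would assess.** This also stands. No decision rule in the protocol hangs on a per-term row, and the Fisher values carry no weight in the conclusion.
- **The example counts are invented and perhaps high.** They are assumed. The Adverse Events and AE and SAE Exemptions sections keep most COPD-related events out of AE reporting, so nine patients in one arm with the same reported event may be unlikely. The exemptions leave a mixed set of other events, however, and wording can vary there too. With smaller counts, one or two relabelled events still change a row.
- **Synonym rows in a small table can be spotted and added up.** This is partly true for event counts. Patient counts cannot be added safely across rows, because one patient may appear under two terms. Spotting synonyms once the arms are in view is also the unblinded grouping that should be avoided.
- **The protocol does not say that whoever chooses the terms knows the arm.** Correct. It is an inference from the non-blinded design, the display of the arm to study staff and the absence of any blinded step for AEs. A reader might go further and infer that wording will in fact favour one arm. Nothing in the document shows that.
- **Coding detail belongs in the statistical analysis plan.** Often it does. Here the protocol has itself made the decision, and a plan that follows it inherits the exclusion of a dictionary. A plan could still add a short category list within the present wording, so the repair is easy.

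**Conclusion.** The point holds for the per-event rows by arm and no further. The protocol fixes a table that needs consistent terms, rules out a dictionary and describes no substitute, in a trial where nothing described shields the choice of term from knowledge of the arm. It holds whether *recoded* is taken literally or as a misprint.

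On size, under assumed counts at 30 per arm, a 20-point difference on one row can read as 6.7 points on each of three rows, and equal rates can read as 20% v 6.7%. Total AEs, total SAEs, patients with any event, the feasibility endpoints, the other effectiveness outcomes and the variance estimates for the definitive trial are untouched. No planned test is affected.

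The conclusion assumes that more than one term will be used for at least some events. The part about knowledge of the arm is inferred from the design and not stated. This is a cheap improvement to a descriptive table and not a threat to the trial's main aims.

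**What to change.** Replace the two sentences on terms in Statistical Methods with text to this effect:

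- Each event is kept as the investigator's verbatim term.
- Before database lock, an existing team member groups the terms from a listing that does not show the arm. The grouping uses a short pre-specified list of body-system categories and terms, or a standard dictionary.
- Events and patients are then tabulated by arm, by category and by grouped term, alongside the totals already planned. Verbatim terms go in a listing.

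The new text should also settle whether *recoded* or *recorded* was meant.

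The cost is a few hours of coding for 60 patients followed for about 90 days, plus the protocol wording. No new data, visits or change in sample size are needed. The downside is the coding effort and the move of verbatim detail from the table to a listing.

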### **Ethical Review and Informed Consent**

This study will be conducted in accordance with ICH GCP guidelines (directive CPMP/ICH/135/95), local regulatory requirements and the declaration of Helsinki, and all relevant local laws and regulations. The protocol and informed consent document will be reviewed and approved by a properly-constituted ethics committee. All aspects of the study will be explained in detail to prospective subjects and they will be informed of the voluntary nature of their participation. Written informed consent will be obtained from each subject using the approved documents, and each subject will receive a copy of his/her signed consents.

### **P.P.I**

Members of Portsmouth and Southampton patient support group Breathe Easy reviewed the Patient Information Sheet (PIS) and informed consent form (ICF). Feedback was positive to the study and all who reviewed the study considered it a worthwhile research project and agreed if they had the opportunity to participate in the study they would.

### **Adverse Events**

An adverse event (AE) is any unfavourable, harmful, or pathologic change in a research subject as indicated by physical signs, symptoms and/or clinically significant laboratory abnormalities.

This includes intercurrent illnesses, injuries, worsening of pre-existing conditions, and events. Stable pre-existing conditions and/or elective procedures to address them are not adverse events. Clinical laboratory findings are considered to be adverse events if regarded as clinically significant by the Investigator, or if these cause (or should have caused) a further diagnostic evaluation, or institution of any therapy.

All events fulfilling any part of the AE definition must be recorded in the source documents and on the adverse event CRF.

Note signs and symptoms of COPD in this study will not routinely be considered to be adverse events unless considered to be so by the PI.

**Serious Adverse Events**

A serious adverse event (SAE) is any adverse event that results in any of the following outcomes: (a) death; (b) an immediate threat to life; (c) inpatient hospitalization or prolongation of an existing hospitalization; (d) persistent or significant disability/incapacity; or (e) a congenital anomaly/birth defect.

Important medical events that do not result in one of these outcomes, but, based on appropriate medical judgment and that are deemed to jeopardize the subject or require medical or surgical intervention to avert one of the listed outcomes, may also be considered SAEs.

**AE and SAE Exemptions**

AE's and SAE's exempt from reporting because it is considered to be part of the expected change in COPD control or an exacerbation or in the judgement of the PI is clinically insignificantly to the patient (i.e Has not caused them harm)

Adverse events exempt from reporting include:

- Increase in rescue medication
- Additional course of steroids and or antibiotics for COPD exacerbation
- Increased unscheduled Healthcare usage (GP and Ed visits for deterioration in COPD control)
- Time off work for due to worsening COPD control
- Hospitalisation due to COPD exacerbation
- Increase in the number or intensity of COPD exacerbations.

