### **Background and Significance**

COPD is characterised by airflow obstruction that is not fully reversible. The airflow obstruction is usually progressive in the long term and results in the gradual development of limiting symptoms such as cough and breathlessness. Cigarette smoking is the predominant cause of COPD, but other factors, particularly occupational exposures, may also contribute to the development of COPD. Exacerbations occur when there is a rapid and sustained worsening of symptoms beyond normal day-to-day variations, these are often associated with acute respiratory infections and can result in unscheduled health care use and hospitalisation.

There are currently 900,000 patients diagnosed with COPD in the UK. COPD is the second leading cause for hospital admission in the UK; recent figures show that one in three people with COPD is readmitted within 28 days of discharge. The latest Quality Standards for COPD from the National Institute for Health and Care Excellence (NICE) highlights the importance of self-management for patients and recommends that every person diagnosed with COPD be given an individualised comprehensive self-management plan. Self-management has been shown to be associated with health service utilisation by COPD patients, improve their quality of life and reduce hospitalisation.

Patients with COPD are often prescribed a complex combination of inhaled medications in a variety of devices; these medications differ enormously in their delivery method and periodicity. This complexity contributes to poor compliance and therefore wasteful prescribing and it is estimated that there is currently only at best a 30% compliance to COPD medications.

The majority of COPD action plans are delivered in a written (paper) format, and currently a validated online interactive solution does not exist. *MyCOPD* has been designed and programmed by my mhealth Ltd with patient and clinician involvement. It is a web-based self-management system designed to encompass the principles of supporting self-care in people with COPD. The system can be easily and securely accessed online by patients and healthcare

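### COPD admissions are exempt from AE/SAE reporting and named in no outcome list, so the safety comparison may not show hospitalised exacerbations

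*Protocol*

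**What the plan says.** Three neighbouring sections of the protocol govern the same event.

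- **Adverse Events** counts the worsening of an existing condition as an adverse event and states: "All events fulfilling any part of the AE definition must be recorded in the source documents and on the adverse event CRF". A closing note leaves it to the principal investigator whether signs and symptoms of COPD count.
- **Serious Adverse Events** includes among its criteria "inpatient hospitalization or prolongation of an existing hospitalization".
- **AE and SAE Exemptions** removes from reporting events regarded as part of the expected course of COPD, and any event that "in the judgement of the PI is clinically insignificantly to the patient". Its list includes "Hospitalisation due to COPD exacerbation", "Increase in the number or intensity of COPD exacerbations", and GP and emergency department visits for COPD deterioration.

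The only safety item under Intervention effectiveness outcomes is "Safety the number of AEs and SAEs by study completion 90(+/- 7) days". Statistical Methods plans one safety analysis: tables of AEs and SAEs by arm, by event and by number of patients. Aims and Objectives promises that the safety of the new intervention will be reported.

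**The concern.** Both arms receive a plan that tells patients when to treat themselves and when to call for help. If such advice goes wrong, one foreseeable result is a COPD exacerbation that ends in hospital. That is the kind of event the exemption list names. If it is left out of the AE/SAE tables and nothing stands in its place, the trial's safety statement says nothing about it.

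There is also a problem of consistency. Two people following the protocol faithfully could produce different SAE tables, one applying the definitions and the other the exemptions. Part of the exemption rests on the investigator's judgement in a trial without blinding; blinded assessment is specified only for the inhaler videos. The arms could then be ascertained differently, although nothing in the protocol shows that they would be.

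**Working it through.** The plan states no figure on this point, so there is none to reproduce. The check is mainly a comparison of sections.

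**1. Is a COPD admission an SAE by definition?** An exacerbation leading to admission is a worsening of an existing condition (Adverse Events) and involves an inpatient stay (Serious Adverse Events). On the definitions it qualifies, subject to the investigator's discretion over COPD signs and symptoms.

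**2. What does the exemption remove?** The protocol does not define *reporting*.
- Reading A: the event is recorded and tabulated but not reported onward. This fits the duty in Adverse Events to record everything.
- Reading B: the event does not enter the AE/SAE data at all. This fits Appendix 1, where the row for AE and SAE *reporting* marks collection at Visits 2, 3 and 4.

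The text does not settle which is meant.

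**3. Does another outcome show the admission?**
- Number of exacerbations and time to exacerbation are listed as effectiveness outcomes, so an admitted exacerbation can be counted there.
- Exacerbation History defines the event by need for oral antibiotics and/or oral steroids and has no grade for severity or admission. A home-treated and a hospitalised episode look the same.
- Antibiotic and steroid use are also listed; neither identifies an admission.
- The exploratory outcome on seeking health care is qualitative.
- The Synopsis, the Feasibility endpoints and Statistical Methods name neither admissions nor emergency department attendances.

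**4. Are the data collected?** Yes. The monthly calls record unscheduled care, GP visits and emergency department attendances. The Admission History section collects admissions and readmissions, checked against GP or other source records. Appendix 1 has rows for both health care usage and admission history.

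**5. Scale, for illustration only.** Inputs: 60 participants, 30 per arm (Sample size rationale), and an assumed 90-day proportion *p* with at least one COPD admission, equal in both arms, with no loss to follow-up.
- Expected participants affected: 60 × p
- Chance of at least one: 1 − (1 − p)^60
- Approximate 95% half-width for the difference between arms: 1.96 × √(2p(1 − p)/30)

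| Assumed p | Expected of 60 (per arm) | Chance of at least one | Half-width |
|---|---|---|---|
| 10% | 6 (3) | 99.8% | 15 points |
| 20% | 12 (6) | over 99.9% | 20 points |
| 33% | 20 (10) | over 99.9% | 24 points |

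For example, at 10%: 1 − 0.9^60 = 0.998, and 1.96 × √(2 × 0.1 × 0.9/30) = 0.152. At each assumed rate some admissions are almost certain. The comparison between arms would be imprecise even when shown, so the gain is that the events become visible, not that a difference could be tested.

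**The case against.** The case on the other side has real weight.

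- **The exemption may be harmless.** Waiving onward reports of expected disease events is not in itself an error. If *reporting* means only that, the events are still recorded and can be tabulated. This stands as a possible reading, and it is why the conclusion says *may*. It does not remove the need to reconcile the three sections.
- **Exacerbations are compared between arms anyway.** Their number and timing are outcomes, and time to exacerbation has a planned analysis. This stands: what is lost is the identification of the admission and its place in the safety comparison, not the exacerbation itself.
- **The analysis plan could add the table.** It could, and no data are lost. But the protocol does more than leave a detail open: it states an exclusion rule that conflicts with its own definitions. The point rests on that rule.
- **The advice is nearly the same in both arms.** The action steps in Appendix 3 match closely, including the trigger for calling the GP or 999, so a difference in harm is not demonstrated. This stands. Delayed care is a foreseeable harm to look for, not a shown one.
- **This is a feasibility trial.** It has no primary outcome, its analysis is largely descriptive, and it says itself that it is underpowered. That lowers the severity, but a descriptive safety table still has to contain the relevant events.

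**Conclusion.** The point holds and should be fixed. The three safety sections conflict. Read as written, they allow a COPD admission to be missing from the AE/SAE table while no named outcome shows it as an admission. This rests on the undefined word *reporting*; under the narrower reading the events would be in the table after all. The size cannot be taken from the documents; 6 to 20 of 60 follows only from the assumed range of 10% to 33%.

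A reader might infer three stronger things that the documents do not support:

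- *That a COPD admission is counted nowhere.* It can enter the exacerbation count and the time-to-exacerbation outcome.
- *That deaths and all admissions drop out of safety.* Death is a criterion of seriousness and is not on the exemption list. Admissions for other causes also remain SAEs.
- *That 20 of 60 participants would be readmitted during the trial.* The Background says "one in three people with COPD is readmitted within 28 days of discharge", and 60/3 = 20. But that rate runs from discharge, states no cause, and starts before randomisation at Visit 1, planned within two weeks of discharge (+/- 1 week). Under an assumed constant hazard, the rest of the 28 days would hold 60 × (1 − (2/3)^(14/28)) ≈ 11 if Visit 1 is on day 14, and 60 × (1 − (2/3)^(7/28)) ≈ 6 if it is on day 21. Some recruits were treated in primary care and never admitted. No 90-day rate is given.

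**What to change.** 1. Reconcile Adverse Events, Serious Adverse Events and AE and SAE Exemptions: state that the exemption concerns onward or expedited reporting only, and that exempt events are still recorded and tabulated.
2. In Intervention effectiveness outcomes and Statistical Methods, name hospital admissions (COPD-related and all-cause) and emergency department attendances as outcomes, summarised by arm as events and as patients, beside the AE/SAE table.
3. Show any investigator label of *expected* or *clinically insignificant* as a category within the tables, not as a reason to leave an event out.

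The cost is a wording amendment and one extra table from data already collected. Displayed event counts will be higher, which the report should explain. No additional onward reports are created.
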